## **2.7 Data Collection**

### **2.7.1 Collection of capillary blood samples and point-of-care test procedures**

The capillary blood samples will be obtained using a lancet to finger prick the middle finger and collect a 1-10 drops of capillary blood. A capillary blood drop will be transferred to the

specimen well of a point-of-care (POC) test (COVID-19 IgG/IgM Rapid Test Cassette, Orient Gene Biotech Co.) using a plastic dropper (delivered with COVID-19 IgG/IgM Rapid Test kit). Two drops (ca. 80 µl) of Orient Gene Biotech sample buffer will be immediately added to the buffer well, with avoidance of air bubbles. If the red colour does not move across the test window or if blood is still present in the specimen well after two minutes, one additional drop of sample buffer should be added into the buffer well. The result should be read in 10 minutes, positive test results may be visible as soon as 2 minutes. The result cannot be interpreted after 15 minutes.

The results of the COVID-19 IgG/IgM Rapid Test Cassette should be interpreted as following:

- **Negative:** The coloured line in the control region (C) changes from blue to red. No line appears in the test line region M or G.
- **Anti-COVID-19 IgM positive:** The coloured line in the control region (C) changes from blue to red and a line appears in the test line M.
- **Anti-COVID-19 IgG positive:** The coloured line in the control region (C) changes from blue to red and a line appears in the test line G.
- **Anti-COVID-19 IgG and IgM positive:** The coloured line in the control region (C) changes from blue to red and a line appears in the test line G and M.
- **Invalid test:** Control line is still completely or partially blue and fails to completely change from blue to red. Insufficient specimen sample or incorrect procedural techniques are the most likely reasons for control line failure. The test should be repeated using a new cassette.

For the study any positive result of IgM or IgG will be considered as a positive result. In case of an invalid test, the test is repeated. When it is still invalid it will be noted as such. Additionally, a few drops of capillary blood will be collected on Dried Blood Spot (DBS) collection cards for (semi-)quantitative analysis of vaccine-induced/infection-induced anti-SARS-CoV-2- specific antibodies as a part of the sub-study performed by Ghent University (details are provided in appendix 6.4).

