For vaccinated NH residents only, a survival analysis will be performed to investigate the proportion of deaths within the study follow-up and the time (in days) to a confirmed COVID-19 death since 14 days after being fully vaccinated (full dose regimen). The survival or censoring time (in days) is registered since 14 days after being fully vaccinated until first event (or censoring moment). A non-COVID-19 related death will be considered as a competing risk in the analysis. If the proportional hazard assumption holds, a stratified (by NH) Cox proportional hazards regression model will be used to model the cause-specific hazards between seropositive and seronegative residents. The latter will be included as a time-varying covariate. A history of self-reported SARS-COV-2 infections, a time-varying NH vaccination degree, province, age, gender, care profile, and presence of COVID-specific comorbidities will be

considered for model adjustment.

7. To assess the duration of SARS-CoV-2 specific antibody response (seroreversion/no antibody response) since 14 days after being fully vaccinated among NH residents and staff in Belgium.

The duration of SARS-CoV-2 specific antibody responses among NH residents and staff in Belgium will be modelled by means of an interval-censored survival analysis. Seroreversion will be defined as a negative rapid test result after at least one positive rapid test result or as two succeeding negative test results (implying the participant did not seroconvert after vaccination within two to four months). The time interval to seroreversion/no response is the time interval between 14 days after the (second) vaccination date (full dose regimen) and the first test moment of a negative test result after at least one positive rapid test or of the two succeeding negative rapid test results. As a sensitivity analysis, the event will also be defined as two succeeding negative rapid test results (whether or not after at least one positive rapid test result), if the rapid test result would turn out to be unstable.

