If the proportional hazard assumption holds, a stratified (by NH) Cox proportional hazards regression model will be used to model the cause-specific hazards between vaccinated and

non-vaccinated residents, adjusting for history of self-reported SARS-COV-2 infections, and a time-varying NH vaccination degree. Propensity score methods will be applied to reduce the effects of confounding.

10. To assess the duration of SARS-CoV-2 specific antibody responses (seroreversion/no antibody response) since self-reported infection in a non-vaccinated residents/staff.

If sufficient non-vaccinated participants with self-reported infection would be available in the random selected sample, a survival analysis for interval censored data will be performed to investigate the time (in days) to a SARS-CoV-2 specific seroreversion/no antibody response since self-reported, natural SARS-CoV-2 infection. A participant is considered to have an event (seroreversion/no antibody response) during the interval between a positive and a negative rapid test result during the follow-up visits, or between the between the positive test date and the first visit date in case of a negative rapid test at the first test date. If the rapid test results would turn out to be unstable, a sensitivity analysis will be performed and an event is considered after two succeeding negative rapid test results during the follow-up study visits. The survival or censoring time will be expressed as an interval in days between the positive test date until the visit date with first event (or censoring moment). A Cox proportional hazards regression model for interval censored data will be used to model the hazard of a SARS-CoV-2 specific seroreversion/no antibody response since natural infection adjusted or stratified for staff and residents.

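### Objectives 7 and 10 time the loss of response on an any-line (IgM or IgG) result, so a remaining or new IgM line can hide or delay the loss of the IgG line

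*Protocol*

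**What the plan says.** Section 2.7.1 lists separate valid readings for the cassette. IgM positive means that "a line appears in the test line M", and IgG positive means that "a line appears in the test line G". Both lines together form a further category. For a negative test it says: "No line appears in the test line region M or G". It then sets one rule: "For the study any positive result of IgM or IgG will be considered as a positive result".

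Section 3.2, objective 7, builds the duration endpoint on that result: "Seroreversion will be defined as a negative rapid test result after at least one positive rapid test result". It adds a second limb, two succeeding negative results, to capture people who never responded. In objective 10 the event falls "during the interval between a positive and a negative rapid test result during the follow-up visits", or before the first visit if the rapid test is already negative there. Both objectives call the endpoint seroreversion or no antibody response. Neither names an antibody class, so the study-wide rule applies.

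Each objective has one sensitivity analysis, to be used if the rapid test proves unstable. Objective 7: "As a sensitivity analysis, the event will also be defined as two succeeding negative rapid test results". Objective 10: "an event is considered after two succeeding negative rapid test results during the follow-up study visits". Both rest on the same composite result. Section 2.7.3 says the interpreted test result is documented, but not that the two lines are stored separately. The dried blood spot ELISA in Appendix 6.4 is not tied to either objective.

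**The concern.** An any-line rule can serve a survey of who has antibody now. Objectives 7 and 10 ask how long a response lasts, and for that the composite works badly. It turns negative only when both lines have gone. An M line that outlasts the G line, appears later, or is a stray reading keeps the participant in the positive state after the G line has disappeared.

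The resulting curve gives the time until neither line is visible. A reader will probably take it as the time until IgG is lost, and for anyone with a remaining M line the two differ. The protocol's background section calls it crucial to assess how long the vaccine-induced response persists, so an overstated duration bears on a main reason for the study.

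**Working it through.** The plan states no figure to reproduce. The check compares the event rules reading by reading, using the four valid readings in section 2.7.1 (negative, M only, G only, both) and the event clauses in section 3.2, non-response limbs included.

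**Step 1. Selected runs of readings at successive visits.**

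| Readings | Any-line rule | Same clauses read on the G line |
|---|---|---|
| G, negative | event at visit 2 | event at visit 2 |
| both, G | no event | no event |
| G, M, negative | event at visit 3 | event at visit 2 |
| both, then M at every later visit | no event | event at visit 2 |
| M, negative | event at visit 2, labelled seroreversion | objective 7: event from two succeeding negatives at visits 1 and 2 (non-response); objective 10: event by visit 1 |

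Rows 3 and 4 show the masking: the event is late or absent. Row 2 shows that a fading M line does no harm while G remains. In row 5 the label changes, but there is an event either way.

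**Step 2. All possible runs.** Six visits with four readings give 4^6 = 4,096 sequences. Applying the same clauses to the any-line result and to the G line, the any-line rule gave an extra event in 0 sequences and an earlier event in 0. This held for objective 7, with the two-negatives limb dated at the first or the second negative, and for objective 10. Every difference was an any-line event that came later or not at all.

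The reason is that every any-line negative is also a G-line negative. For objective 7, suppose the any-line rule gives an event at visit k. If a G line was seen earlier, visit k is a G-line negative after a positive. If none was seen, visits k-1 and k are two succeeding G-line negatives. In both cases the G-line event has occurred by visit k. For objective 10, a missing G line at the first visit is already an event.

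**Step 3. The sensitivity analyses.** Under the two-negatives rule, both-M-M is still no event, although the G line was absent at two visits in a row. G-M-negative-negative is an event, but its two negatives are visits 3 and 4, whereas the G line was already absent at visits 2 and 3. The masking remains.

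**Step 4. Size, under assumptions.** Let g be the share losing the G line in one interval and h the share of those who show an M line at that visit. The protocol gives neither. The any-line rule counts g × (1 − h) on time.
- g = 5%, h = 0 to 30%: 5% × 1 = 5% down to 5% × 0.70 = 3.5%.
- g = 20%, h = 0 to 30%: 20% down to 20% × 0.70 = 14%.

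The masked participants (0 to 30% of those losing G, as assumed) are dated at least one visit later, 60 days on the planned schedule, or never.

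**The case against.** The strongest defence is that nothing is contradicted. The objectives speak of SARS-CoV-2 specific antibody responses without naming a class, the any-line rule is set explicitly for the whole study, and it is applied consistently. The sensitivity of 92.9% and specificity of 96.3% in section 4.3 are not split by line, so a G-line endpoint has no stated test performance. A class-specific sensitivity analysis could also sit in a separate analysis plan. The first three points stand, and they make this a question of marker choice. The last carries less weight, because the protocol itself fixes the event definition and its sensitivity analyses, and lines that were not recorded cannot be recovered later.

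The preference for G also rests on the usual understanding that IgG is the longer-lasting class, which the protocol does not state. The masking does not depend on that premise. It follows from the definitions wherever an M line shows after G has gone.

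A reader might infer a stronger point: that a passing M-only reading followed by a negative creates false events and shortens the reported duration. The documents do not support this. Both objectives count non-response as an event, so such a participant is an event on the G line too, at the same visit or earlier. Any inflation factor obtained by treating these participants as event-free compares the plan with a different endpoint, seroreversion among G-line responders only.

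**Conclusion.** The point holds in one direction. With the endpoint as written, the any-line rule can delay or miss loss of the G line and cannot add or advance an event, so the reported duration is, if anything, too long. An M-only reading followed by a negative is mislabelled as seroreversion when it would be non-response on the G line, but it is an event on either reading.

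The size is unknown. It depends on how many participants show M after losing G, and it is nil if none do. The step 4 range is an illustration, not an estimate. The conclusion assumes that the study wants the duration of the IgG response. If any detectable antibody is truly the target, the composite matches it, and the protocol should say so. The change is worth making because it is cheap and the planned sensitivity analyses do not cover the problem.

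**What to change.** 1. In section 2.7.3, state that the M and G lines are recorded separately for every test.
2. In section 3.2, define response and seroreversion for objectives 7 and 10 on the G line. At minimum, pre-specify this analysis beside the composite.
3. Keep the non-response limbs: two succeeding negatives in objective 7, and a negative first visit in objective 10.
4. Treat an early M-only reading as not yet evaluable until the next visit, so that it counts neither as a response nor as a failed response. This goes beyond the straight G-line comparison in the working. In objective 7, for example, M-negative followed by G at every later visit is an event under the any-line rule and would no longer be one. It should therefore be written as an explicit rule.
5. Report the any-line version alongside, and keep it for the seroprevalence objectives.

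No new test or visit is needed, since both lines are already read on every cassette. The costs are a recording field, a wording change and one further analysis. There are two limits. The quoted test performance is not split by line, and if completed rounds stored only an overall result, the G-line analysis may not be recoverable for them.

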### **Tertiary objectives**

Although this study was not designed to assess vaccine effectiveness, end points will be compared between vaccinated and non-vaccinated participants, applying propensity score methods, if sufficient non-vaccinated participants occur in the random selected sample.

8. To assess the risk of getting SARS-CoV-2 infected between vaccinated and non-vaccinated (at last visit) residents/staff.

If a sufficient number of non-vaccinated participants are available in the sample, a survival analysis will be performed to investigate the time (in days) to a SARS-CoV-2 infection

since 14 days after being fully vaccinated between vaccinated and non-vaccinated participants. A participant is considered to have an event when the participant had a reported positive PCR test result (or a positive antigen rapid test, or a positive CT scan, or a positive saliva test in absence of a PCR test) during the baseline or one of the follow-up visits. The survival or censoring time (in days) is registered since 14 days after being fully vaccinated (or since 14 days after main (second) vaccination date in corresponding NH in case of non-vaccinated participants) until first event (or censoring moment).

If the proportional hazard assumption holds, a stratified (by NH) Cox proportional hazards regression model will be used to model the hazard of SARS-CoV-2 infection between staff and residents, and between vaccinated and non-vaccinated participants, adjusting for history of self-reported SARS-COV-2 infections, and a time-varying NH vaccination degree. Propensity score methods will be applied to reduce the effects of confounding. If insufficient non-vaccinated residents would be available in the cohort, the analysis will be performed for staff only.

9. To assess the proportion of confirmed COVID-19 deaths and non-COVID-19 related deaths and the time until death (within the study timeframe) between vaccinated and non-vaccinated residents.

If sufficient non-vaccinated residents would be available, a survival analysis will be performed to investigate the time (in days) to a confirmed COVID-19 death since 14 days after vaccination (or since 14 days after main (second) vaccination date in corresponding NH in case of non-vaccinated participants). A non-COVID-19 related death will be considered as a competing risk in the analysis.

If the proportional hazard assumption holds, a stratified (by NH) Cox proportional hazards regression model will be used to model the cause-specific hazards between vaccinated and

non-vaccinated residents, adjusting for history of self-reported SARS-COV-2 infections, and a time-varying NH vaccination degree. Propensity score methods will be applied to reduce the effects of confounding.

10. To assess the duration of SARS-CoV-2 specific antibody responses (seroreversion/no antibody response) since self-reported infection in a non-vaccinated residents/staff.

If sufficient non-vaccinated participants with self-reported infection would be available in the random selected sample, a survival analysis for interval censored data will be performed to investigate the time (in days) to a SARS-CoV-2 specific seroreversion/no antibody response since self-reported, natural SARS-CoV-2 infection. A participant is considered to have an event (seroreversion/no antibody response) during the interval between a positive and a negative rapid test result during the follow-up visits, or between the between the positive test date and the first visit date in case of a negative rapid test at the first test date. If the rapid test results would turn out to be unstable, a sensitivity analysis will be performed and an event is considered after two succeeding negative rapid test results during the follow-up study visits. The survival or censoring time will be expressed as an interval in days between the positive test date until the visit date with first event (or censoring moment). A Cox proportional hazards regression model for interval censored data will be used to model the hazard of a SARS-CoV-2 specific seroreversion/no antibody response since natural infection adjusted or stratified for staff and residents.

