10. Indien van toepassing, bent u gevaccineerd met een vaccin tegen COVID-19?  
 Zo ja, datum van de uw vaccinatie. (*Deze vraag zal ingevoerd worden zodra van toepassing*)

***Vaccine hesitancy bij medewerkers van woonzorgcentra in België: éénmalige vragenlijst als onderdeel van de follow-up vragenlijst***

A . Bent u reeds gevaccineerd tegen COVID-19?

- Ja, ik ben reeds gevaccineerd (1 of 2 dosissen)
  - Heeft u getwijfeld voor u hebt besloten zich te laten vaccineren? Ja/nee
    - Indien ja → vraag B + C
    - Indien nee → einde vragenlijst
- Ik word binnenkort gevaccineerd
  - Heeft u getwijfeld om zich te laten vaccineren? Ja/nee
    - Indien ja → vraag B + C
    - Indien nee → vraag D
- Ik twijfel of ik me zou laten vaccineren
  - Vraag B
- Ik heb besloten om me niet te laten vaccineren
  - Vraag E

B . Wat is de hoofreden waarom u twijfelt/twijfelde om gevaccineerd te worden tegen COVID-19?

- Ik ben/was bezorgd over onbekende toekomstige effecten van het vaccin
- Ik ben/was bezorgd over de bijwerkingen van het vaccin
- Ik vertrouw/vertrouwde vaccinaties niet.
- Ik heb/had het idee dat het onwaarschijnlijk is dat ik ernstig ziek zal worden van het coronavirus
- Ik vind/vond dat de impact van het coronavirus wordt overdreven
- Ik denk/dacht dat het vaccin niet kan verhinderen dat ik besmet zal geraken met het virus
- Ik heb een aandoening waardoor het vaccin niet veilig is voor mij
- Ik ben reeds besmet geweest met COVID-19 dus ik heb geen vaccin nodig
- Ik ben bang van naalden
- Ik heb geen mensen in mijn omgeving die tot de risicogroep behoren
- Anders : \_\_\_\_\_ (deelnemers krijgen een invulveld)
- Ik verkies niet te antwoorden

C. Wat is de hoofreden waarom u besloot u toch te laten vaccineren?

- Ik vond de resultaten van de eerste vaccinaties geruststellend
- Ik had meer tijd nodig om me te informeren
- Een vriend/ familielid/ gezondheidsprofessional heeft het mij aanbevolen
- Iemand uit mijn omgeving werd ernstig ziek van het coronavirus
- Ik voelde de nood om te laten vaccineren om andere kwetsbare mensen te beschermen tegen het virus
- Ik ben bang dat ik zonder vaccinatie niet meer zal kunnen reizen
- Ik denk dat het vaccin deze gezondheidscrisis zal oplossen
- Ik voelde me onder druk gezet door mijn professionele omgeving
- Ik voelde me onder druk gezet door familieleden/vrienden
- Ik volgde de overheidsaanbeveling om me te laten vaccineren (veiligheidsraad, sensibilisering affiches, etc.)

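### Tertiary objectives 8 and 9 discard the unvaccinated time of people vaccinated later, which biases the death comparison toward vaccine benefit and can bias the infection comparison in either direction

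*Protocol*

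**What the plan says.** Objectives 8 and 9 of protocol section 3.2 are the first two tertiary objectives of section 2.1.

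- **Groups, objective 8 (infection):** "To assess the risk of getting SARS-CoV-2 infected between vaccinated and non-vaccinated (at last visit) residents/staff". Section 2.1 has the same parenthesis.
- **Start of time, vaccinated, objective 8:** "The survival or censoring time (in days) is registered since 14 days after being fully vaccinated".
- **Start of time, non-vaccinated, both objectives:** "since 14 days after main (second) vaccination date in corresponding NH in case of non-vaccinated participants".
- **Start of time, vaccinated, objective 9 (death in residents):** the aim is to "investigate the time (in days) to a confirmed COVID-19 death since 14 days after vaccination". The requirement of full vaccination is not repeated, and nothing says when vaccination status is read.
- **Model:** Cox regression stratified by home, "adjusting for history of self-reported SARS-COV-2 infections, and a time-varying NH vaccination degree", and "Propensity score methods will be applied to reduce the effects of confounding".

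In both objectives the home's vaccination coverage varies with time, but the individual's own vaccination status does not. Objectives 5 and 6 of the same section do treat an individual characteristic, seropositivity, as time-varying.

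**The concern.** Consider a resident who is unvaccinated when the home completes its second round. If this resident dies before being vaccinated, the death and the time before it count as non-vaccinated. If the resident survives and is vaccinated later, they become a vaccinated participant whose time starts 14 days after their own full vaccination. The months survived unvaccinated then count nowhere. The non-vaccinated group keeps its deaths and loses event-free time, so its death rate is too high even if the vaccine does nothing.

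For infection the same deletion removes both the time and any infection that occurred before the later vaccination. Whether this distorts the comparison depends on whether infection changes the chance of being vaccinated afterwards.

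Propensity scores and adjustment for earlier infection deal with differences between people. They do not restore time that the grouping rule has deleted.

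Late vaccination is foreseen. The follow-up forms ask again about vaccination after a previous no, and the staff hesitancy form offers an answer for those about to be vaccinated. Section 4.4 sends results to public health authorities and the press, where a spurious protective hazard ratio could be read as vaccine effectiveness.

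**Working it through.** The protocol states no figure for these objectives, so there is none to reproduce. The check asks what the rules return when the true hazard ratio is 1.

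**Inputs**
- T = 300 days of follow-up (section 2.4).
- 15% unvaccinated at the start: the share of staff found at the first test round (table of changes). Used in the simulations only.
- Assumed: the share v of the initially unvaccinated who are vaccinated by day 300 if still alive, and mortality m. Section 2.5 gives resident drop-out of 0.4 but not how much of it is death.

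**Death, closed form with constant hazards**
- Hazards: h = −ln(1−m)/T, r = −ln(1−v)/T, s = h + r.
- Deaths counted as non-vaccinated, per initially unvaccinated person: D = (h/s)(1 − e^(−sT)).
- Mean time to those deaths: μ = 1/s − T·e^(−sT)/(1 − e^(−sT)).
- Time counted as non-vaccinated: PT = T·e^(−sT) + D·μ.
- The vaccinated group shows the true hazard h, so the apparent hazard ratio is h/(D/PT).

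Example with m = 20%, v = 50%:
- h = 0.000744, r = 0.002310, s = 0.003054, e^(−sT) = 0.8 × 0.5 = 0.4.
- D = (0.000744/0.003054) × 0.6 = 0.1461.
- μ = 327.4 − 200.0 = 127.4 days.
- PT = 120 + 0.1461 × 127.4 = 138.6 days.
- Rate = 0.1461/138.6 = 0.001054, which is 1.42 times h. Apparent hazard ratio 0.71.

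If unvaccinated time were kept until vaccination, PT would be 0.6/0.003054 = 196.4 days and the rate 0.1461/196.4 = 0.000744, exactly h. The whole bias is the missing 57.8 days per person.

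| Vaccinated later (assumed) | D | PT (days) | Rate ÷ h | Apparent HR |
|---|---|---|---|---|
| 10% | 0.1902 | 243.0 | 1.05 | 0.95 |
| 20% | 0.1800 | 217.0 | 1.12 | 0.90 |
| 25% | 0.1747 | 204.0 | 1.15 | 0.87 |
| 50% | 0.1461 | 138.6 | 1.42 | 0.71 |

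At 10% or 30% mortality the hazard ratios change by 0.01 at most. If confirmed COVID-19 deaths are a constant fraction of all deaths, that fraction cancels and the ratios are unchanged.

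**Cox simulation** (2 million people per scenario, one common home date, no propensity score). For death it gives 0.94–0.95, 0.90–0.91, 0.82 and 0.71 at 10, 20, 33 and 50% late vaccination.

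**Infection, constant incidence**
- Infection does not affect uptake: 1.00.
- Half to all infected people then stay unvaccinated, 25% vaccinated late: 0.93 to 0.87.
- Infection halves the later vaccination rate: 0.94 at 20% late vaccination, 0.84 at 50%.
- Infection doubles it: 1.12 at 20%, 1.37 at 50%.

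**Different start dates alone** (infection not affecting uptake, 20 to 67% late vaccination): 0.95–0.99 with falling incidence, 1.01–1.05 with rising incidence, 1.00 with constant incidence.

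**Both together, infection halving uptake:** 0.91 at 20% and 0.75 at 50% with falling incidence; 0.99 and 0.95 with rising incidence.

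**Repair:** time-varying vaccination on one clock returned 0.99 to 1.01 in every scenario in which it was run (death with constant hazard; infection with falling, rising and U-shaped incidence, uptake unaffected).

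**The case against.** Several stronger readings are tempting, and the protocol does not support them.

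- **That both objectives read status at the last visit.** The words are printed for objective 8 only. For objective 9, the object of the death figures, the problem is inferred from fixed groups and the clock rule. If status there were fixed at the start of follow-up, with late vaccinees censored when vaccinated, this bias would not arise. The text does not say so.
- **That the hazard ratio is always pushed toward protection.** This is structural for death only. For infection it depends on behaviour and can reverse.
- **That the protocol shows infection deterring vaccination.** The hesitancy item "Ik ben reeds besmet geweest met COVID-19 dus ik heb geen vaccin nodig" (already infected, so no vaccine needed) is one option on a one-off staff form. It covers infection at any time and says nothing about residents. It makes deterrence plausible, not established.
- **That the two start dates are a defect of equal weight.** Anchoring non-vaccinated people to their home's campaign is a reasonable index date. For people vaccinated in the main round the dates largely coincide.
- **That vaccinated people are credited with their earlier unvaccinated time.** It is dropped, not reassigned.

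It is also fair that objective 9's missing reference to full vaccination looks like shorthand, that the late-vaccinated share is unknown, and that section 3.2 says the study was not designed for vaccine effectiveness. These points lower the weight. They leave intact that objective 8 prints a grouping rule based on the future, and that neither adjustment nor propensity scores restore the lost time.

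**Conclusion.** The point holds in limited form. Objective 8's printed rule, and objective 9's clock rule with fixed groups, drop the unvaccinated time of people vaccinated later.

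For death, with no true effect, the hazard ratio is about 0.95 to 0.90 if 10 to 20% of the initially unvaccinated are vaccinated later, and about 0.71 if 50% are. This assumes constant hazards and reads objective 9 as counting later vaccinees as vaccinated from their own start date.

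For infection the grouping does no harm if infection leaves uptake unchanged. At 25% late vaccination the hazard ratio is about 0.93 to 0.87 if half to all infected people stay unvaccinated, and the bias runs the other way if infection increases uptake. The different start dates alone move it only to about 0.95–1.05.

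The analyses are tertiary and run only if enough non-vaccinated participants are available, so the severity is modest. The change is still worth making before analysis.

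**What to change.** 1. Delete the parenthesis about the last visit from objective 8, in sections 2.1 and 3.2.
2. In objectives 8 and 9, model individual vaccination as time-varying: unvaccinated until the first dose; partly vaccinated or less than 14 days after the full regimen; fully vaccinated for at least 14 days. Use one common time scale (calendar date or days since the home's second round) and keep the stratification by home.
3. Make objective 9's start for vaccinated residents refer to full vaccination, as in objective 8.
4. For deaths, use delayed entry at the baseline visit, since participants had to be alive to enrol. The campaign began on 5 January 2021 and Table 1 puts first sampling in February, so some clocks can start before enrolment. For infections, delayed entry would discard events reported at baseline, which objective 8 counts, so run it as a sensitivity analysis.

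**Cost:** a counting-process data set, plus full-regimen dates. The protocol's own clock already needs those dates, but the individual forms ask specifically only for the first-dose date; a further follow-up item asks for a vaccination date without naming the dose. Where the individual date is missing, the home's second-round date can stand in. That suits main-round participants. For late vaccinees it can precede their own first dose, so their second-dose date should be obtained directly if possible.
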